### Primary and secondary outcome measures

The primary outcome of this study is the annualized rate of change in eGFR (i.e., eGFR slope), expressed as mL/min/1.73 m² per year. Based on findings from a recent meta–analysis of RCTs, the eGFR slope is recognized as a reliable surrogate endpoint for tracking CKD development [45, 46]. Given that serum cystatin C levels are less influenced by physical activity and muscle mass than serum creatinine levels [47], serum cystatin C levels are used to calculate the eGFR and evaluate changes in kidney function. The eGFR slope is determined using a linear mixed–effects model with random intercepts [48].

The secondary outcomes include alterations in renal hemodynamics and oxygenation assessed using Doppler ultrasound imaging and MRI, glomerular and tubular damage biomarkers, cardiovascular function indices, such as arterial stiffness and endothelial function, blood– and urine–based markers of mineral and bone metabolism, body composition and bone density, muscle strength, cardiorespiratory fitness, physical performance, habitual dietary intake, sedentary behavior, physical activity, sleep quality, and mental health. The detailed measurement methods for the secondary outcomes are provided in the Supplementary Material.

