### Sample size calculation

The sample size calculation for this clinical trial is based on a previous study that explored the impact of a 1–year structured rehabilitation program on kidney function decline among patients with CKD, using a small sample from a TwiCs study design [49]. According to this previous study, the annual slope of eGFR (mL/min/1.73 m²/year) was approximately + 2 in the intervention group and − 3 in the control group, indicating a between–group difference of approximately 5 units per year. Assuming a standard deviation of 8, a two–sided significance level of 0.05, and a statistical power of 0.80, a total of 84 participants would be required based on a two–sample t–test.

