### Statistical analysis

All analyses will be conducted based on the intention–to–treat (ITT) principle. Statistical significance is set at *P* < 0.05. Data are expressed as mean ± standard deviations, median [interquartile range], or frequency counts (%), as appreciate. Baseline group characteristics will be compared using one–way analysis of variance or the Kruskal–Wallis test for continuous variables and the chi–square test or Fisher’s exact test for categorical variables. The eGFR slope for the 6–year pre–intervention, 1–year during–intervention, and 1–year post–intervention phases will be calculated. For calculating the eGFR slope, the repeated measurements of eGFR will be analyzed using a linear mixed model (LMM) including continuous time as a fixed effect and individual participant as a random effect (henceforth, Model 1). In addition, the slope will be estimated using a single linear regression of eGFR on time by each participant (called as Model 2) as a supplementary analysis.

For a primary analysis, the eGFR slope will be compared using the LMM including the group (exercise, stretching, and usual lifestyle), time, their interaction term, and the baseline eGFR as fixed effects and individual participant as a random effect. The eGFR slopes calculated by Models 1 and 2 will also be compared between groups using analysis of covariance, including the group as a factor and the eGFR slope of the 6–year pre–intervention phase as a covariate. The eGFR slope for the 6–year pre–intervention, 1–year during–intervention, and 1–year post–intervention phases will be performed using paired t–tests for within–group comparison.

Secondary outcomes will be analyzed using the generalized estimating equations (GEE) method, including group, categorical time point (baseline, 6 months, and 1 year), and their interaction term as factors. In each model, an unstructured (UN) correlation matrix will be used to account for within–individual correlations across time points. If the UN matrix leads to a convergence problem for numerical optimization, a simpler correlation structure will be used. The results of the GEE analysis will be presented as the marginal means with 95% confidence intervals. Pearson product–moment correlation analysis and repeated–measure correlation analysis [50] will be conducted to examine the associations between individual changes in each outcome.

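### The primary group-by-time model is written with a random intercept only, so with three or more visits its standard error omits half or more of the between-person slope variance and the test exceeds its nominal 5%

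*Protocol article*

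**What the plan says.** In the Protocol article, Primary and secondary outcome measures defines the primary outcome as the annualised change in eGFR and states: "The eGFR slope is determined using a linear mixed–effects model with random intercepts".

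Statistical analysis specifies the primary comparison as a mixed model with group (three levels), time, their interaction, "and the baseline eGFR as fixed effects and individual participant as a random effect". It names no random slope, robust standard error or other covariance structure for the primary outcome. For the secondary outcomes the same section does name an unstructured correlation matrix.

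As a supplementary analysis (Model 2), "the slope will be estimated using a single linear regression of eGFR on time by each participant". Slopes from Models 1 and 2 are then compared between groups by analysis of covariance.

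Sample size calculation treats each participant's slope as a single observation in a two-sample t-test: "Assuming a standard deviation of 8", with a difference given as "indicating a between–group difference of approximately 5 units per year" and a total of 84.

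Measurements lists visits at 0, 6, 12 and 24 months. Statistical analysis does not say which of them enter the primary model.

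**The concern.** A random-intercept model lets people differ in level but assumes that everyone in a group has the same true slope. If slopes do differ, the model treats that variation as visit-to-visit noise and spreads it over all within-person degrees of freedom, instead of charging it to the slope contrast. The standard error of the group-by-time term is then too small, and its confidence interval and P value are too favourable.

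The protocol itself presupposes that slopes differ. The Introduction justifies the design by large individual variation in kidney ageing. The sample size rests on a between-person slope SD. The covariance analysis uses each person's pre-intervention slope as a covariate. The primary test as written is the one place where this variation is not fully counted. At stake is the 5% error rate of the primary exercise-versus-stretching comparison.

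**Working it through.** **1. The plan's own figure.** Inputs from Sample size calculation: difference 5, SD 8, two-sided alpha 0.05, power 0.80. The normal approximation gives 2 × (1.96 + 0.84)² × 8² / 5² = 40.2, so 41 per arm. The exact t-test gives power 0.798 at 41 per arm and 0.808 at 42, so the stated 84 is reproduced. This calculation counts the full variance of a participant's slope, 8² = 64.

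**2. Formulas.** Let s be the residual SD, tau the SD of true slopes, k the number of visits (balanced and complete), and Sxx the sum of squared deviations of visit times in years.

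- True variance of one participant's estimated slope: s²/Sxx + tau².
- Variance implied by the random-intercept model: s²/Sxx + tau²/(k − 1).
- Actual type I error: 2 × [1 − Φ(1.96 × √(model variance / true variance))].

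The share of tau² left out is therefore 1 − 1/(k − 1): one-half for 0/6/12 months (k = 3, Sxx = 0.5), two-thirds for 0/6/12/24 months (k = 4, Sxx = 2.1875), and none for two visits such as 6 and 12 months.

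**3. Assumption.** The documents do not split the SD of 8. For a 0/6/12-month slope, 64 = 2s² + tau². I take s from 5.5 down to 3, and separately a smaller tau of 1 to 3 with s = 5.

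**4. Visits 0, 6, 12 months, exercise versus stretching.**

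| s | tau² | true variance | model variance | SE ratio | type I error |
|---|---|---|---|---|---|
| 5.5 | 3.5 | 64 | 62.25 | 0.986 | 5.3% |
| 5 | 14 | 64 | 57 | 0.944 | 6.4% |
| 4 | 32 | 64 | 48 | 0.866 | 9.0% |
| 3 | 46 | 64 | 41 | 0.800 | 11.7% |
| 5 | 1 | 51 | 50.5 | 0.995 | 5.1% |
| 5 | 9 | 59 | 54.5 | 0.961 | 6.0% |

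With 43 and 45 participants (Table 1), the correct SE at SD 8 is 8 × √(1/43 + 1/45) = 1.71. At s = 4 the model would report √48 × √(1/43 + 1/45) = 1.48. A joint test over all three groups (2 df) is affected more: 6.9%, 10.6% and 14.7% at s = 5, 4 and 3 under the SD-8 split.

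**5. If the 24-month visit were pooled into one straight line.** With the same s and tau:

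- s = 5.5: 17.33 true against 15.00 model, 6.8%.
- s = 4: 39.3 against 18.0, 18.5%.
- s = 3: 50.1 against 19.4, 22.2%.
- s = 5 with tau 1 to 3: 5.7% to 10%.

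**6. Simulation check.** With group sizes 43/45/53 and 4,000 runs, s = 4 and tau = 5.66 gave 8.6% (0-12 months) and 20.2% (0-24 months), against 9.0% and 18.5% in closed form. REML fits of the stated model with the baseline covariate (144 to 204 runs per case) gave the following at s = 3, 4 and 5:

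- 0/6/12 months: 11%, 12%, 8%.
- 0/6/12/24 months: 23%, 16%, 13%.

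With 6 and 12 months only, and s from 2 to 5, the range was 4% to 8%. With about 150 runs, the simulation standard error at 5% is √(0.05 × 0.95 / 150) = 1.8 percentage points, so these small runs support the direction rather than the exact size.

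**The case against.** Several points on the other side have force.

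- **The wording may be loose.** The random-intercepts sentence describes how the slope is determined. The primary comparison says only that the participant is a random effect. A random-intercept-only Model 1 would give every participant the same slope, so the planned covariance analysis and paired t-tests on Model 1 slopes could not be carried out. A random slope may have been intended. That stands as a reason for caution about what will be run. It also shows that the text needs correcting.
- **One reading has no inflation.** Baseline eGFR is a covariate, so only 6 and 12 months might be outcomes. With two visits nothing is left out. The plan does not state this restriction, and a slope for the one-year intervention phase most naturally includes baseline, but the reading is possible.
- **The size rests on assumptions.** At s = 3, tau is 6.8 per year, a very wide spread of true slopes. The SD of 8 belongs to a calculation based on a small CKD study, whereas the Discussion says that this cohort has relatively preserved kidney function. With tau of 1 to 3, the one-year inflation is at most one percentage point. One mixed-model check of 200 runs (s = 4.5, tau = 4.85) gave 7% for 0-12 months, with an exact 95% interval of about 4% to 11.5%, which does not exclude 5%.
- **Model 2 is already planned.** It counts slope variation properly, and a falsely narrow primary interval could be noticed beside it. But it is labelled supplementary and does not protect the primary P value.

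A reader might infer that the model omits most of the slope variance, or that the test always rejects more than 5% of the time. The documents support neither. Over 0/6/12 months the omitted share is exactly half. More than half requires pooling the 24-month visit (or the pre-intervention series) into one line, whereas Statistical analysis treats the pre-, during- and post-intervention slopes separately. The 0-24 month figures should not be read as the expected size.

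**Conclusion.** Wrong as written, and should be fixed; confidence is moderate to high. With three or more visits and any true variation in slope, the stated primary test is anti-conservative, and that direction does not depend on how the SD of 8 is split. For exercise versus stretching over 0, 6 and 12 months, type I error is about 5% to 12% under the plan's SD with residual SD 5.5 to 3, and 5.1% to 6.0% under the smaller slope SDs. It would reach about 6% to 22% only if 24 months were pooled into one straight line, and it stays at 5% if only 6 and 12 months are outcomes. These figures assume balanced, complete visits and a variance split that the documents do not give. What holds without that split is the mismatch: the sample-size t-test and the Model 2 comparison carry the full slope variance, and the primary test as written does not.

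**What to change.** In Statistical analysis, add to the primary mixed model a participant-level random slope for time with a free intercept-slope covariance. As the fallback if it does not converge, name either participant-clustered robust standard errors or the already planned Model 2 slope comparison. State which visits enter the primary model. In Primary and secondary outcome measures, change the description to random intercepts and slopes.

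The cost is a line or two of wording before analysis and a correct, wider interval. Over 0-12 months the standard error is larger by a factor of 1/0.986 to 1/0.800, about 1% to 25%, at SD 8; the smaller-SD cases fall within or just below that range. This takes nothing from the planned power, because the calculation behind 84 participants already uses the full slope SD.

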By using the TwiCs study design, the current study involving middle–aged and older adults aims to investigate whether a 1–year progressive moderate– to high–intensity exercise training program can slow kidney function decline and renal hemodynamics/mineral metabolism deteriorations. The hypotheses for this study are as follows: (1) 1–year of structured exercise training will attenuate the kidney function decline while improving renal hemodynamics and mineral metabolic status. Specifically, we hypothesize that the annualized rate of kidney function decline during the 1–year intervention period will be smaller than the annualized rate observed during the 5–year pre–intervention observational period within the same individuals assigned to the exercise group. (2) Additionally, we hypothesize that increases in physical activity and fitness levels will be positively associated with favorable changes in kidney function. To our knowledge, this study is the first to apply the TwiCs study design in the field of sports nephrology. The current study is expected to provide new insights regarding the effectiveness of nonpharmaceutical interventions for CKD development.

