## Methods

### Study design, procedure, and ethics

The Aging Kidney and Exercise Training Study (AKETS) is a 24–month, community–based, two–arm RCT using the TwiCs study design (Fig. 1) and is conducted within the Aging Kidney Study (AKS) cohort, which started in November 2018 with the aim of investigating the associations between age–related changes in mineral metabolism and kidney health in individuals with and without CKD (UMIN000034741). The AKS cohort is a uniquely comprehensive dataset encompassing physiological, biochemical, behavioral, and physical performance measures relevant to kidney health, enabling multifactorial analyses of potential risk and protective factors associated with age–related kidney function decline. Cross–sectional analyses from the AKS cohort have already identified some novel lifestyle factors of kidney health [38–43], highlighting the potential importance of non–pharmacological strategies to slow kidney function decline. Such preliminary evidence from the AKS cohort provides a strong rationale for conducting the current study. The AKETS protocol includes four assessment time points: baseline, 6 months (midpoint), 12 months (end of intervention), and 24 months (follow–up) (Fig. 1).

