#### Usual lifestyle group (Time control group)

Within the AKS cohort, a group of participants who are followed up without receiving any intervention is designated as the usual lifestyle (i.e., time control) group for this study. The participants who opt for the time control group are instructed to maintain their usual lifestyle habits and encouraged to participate in annual follow–up assessments.

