A key difference between the handful of previous interventional studies examining the effects of exercise training on kidney health in individuals with or without CKD and our study is the fact that our study has the long–term observational data spanning six years before intervention initiation. This difference is important for addressing the clinical question of whether exercise can improve deteriorating kidney health, which has worsened over several years owing to aging and long–term lifestyle disruptions. To our knowledge, only one pilot study has been conducted with a similar design comparing changes in kidney function before and after the intervention, suggesting that exercise training can slow the progressive deterioration in kidney function in patients with CKD [49]. However, this pilot study had a small sample size (*n* = 20) and short pre–intervention follow–up period (one year) and did not conduct follow–up measurements after the intervention. Therefore, we aimed to address these limitations by adopting a better design (i.e., TwiCs) to clarify whether exercise improves, does not affect, or deteriorates kidney health.

Emerging evidence suggests that the deterioration in renal hemodynamics [12] and mineral metabolism [13] observed in early middle age may contribute to the rapid kidney function decline in later life. Based on these findings, preventive measures to minimize the deterioration of renal hemodynamics and mineral metabolism may lead to improved long–term renal outcomes. However, the long–term effects of preventive interventions on renal hemodynamics and mineral metabolism remain unclear. In this study, as a secondary outcome, we comprehensively investigated the effects of long–term structured exercise training on renal hemodynamics and mineral metabolism in middle–aged and older adults. This will allow us to provide new insights into the underlying mechanisms through which exercise training contributes to the suppression of kidney function decline.

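### The ANCOVA covariate (pre-intervention eGFR slope) probably shares the trial-baseline value with the outcome slope, so it under-corrects, and may enlarge, prior-slope differences against the self-chosen group

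*Protocol article*

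**What the plan says.** All references are to the protocol article.

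- **Slopes.** Statistical analysis: "The eGFR slope for the 6–year pre–intervention, 1–year during–intervention, and 1–year post–intervention phases will be calculated". Model 2, a separate linear regression for each participant, is labelled supplementary.
- **The ANCOVA.** Same section: "The eGFR slopes calculated by Models 1 and 2 will also be compared between groups using analysis of covariance". It comes on top of the primary analysis, a linear mixed model with group, time, their interaction and baseline eGFR. The ANCOVA is specified as "including the group as a factor and the eGFR slope of the 6–year pre–intervention phase as a covariate".
- **Trial visits.** Study design, procedure, and ethics gives baseline, 6, 12 and 24 months. A slope for the intervention year therefore starts at the trial baseline.
- **Pre-intervention data.** The Discussion says "our study has the long–term observational data spanning six years before intervention initiation". The cohort is one "which started in November 2018", and the trial was registered in October 2024.
- **A different length.** The Introduction's hypothesis compares with "the annualized rate observed during the 5–year pre–intervention observational period within the same individuals assigned to the exercise group".
- **Groups.** Under Randomization and blinding, participants choose between usual lifestyle and intervention. Only exercise versus stretching is randomised.

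Nowhere does the article list the visits that enter the pre-intervention slope.

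**The concern.** From November 2018 to October 2024 is just under six years. A six-year pre-phase therefore runs up to about the trial baseline, and the baseline eGFR would be both its last value and the first value of the intervention-year slope. A baseline reading that is high by chance makes the earlier decline look slower and the later decline look faster. That negative coupling works against the true positive link between a person's past and future decline, which is the link the covariate is there to use.

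The consequence falls on comparisons with the usual-lifestyle group. Among the planned between-group analyses, this ANCOVA is the only one that adjusts for prior rate of decline. If people who chose usual lifestyle were already declining at a different rate, a coefficient that is too small leaves too much of that difference in the result, and a negative one adds to it. A negative coefficient could also be misread as showing that those who declined fastest before gained most.

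**Working it through.** **Inputs from the article.** Difference 5, SD 8, two-sided 0.05, power 0.80, total 84 (Sample size calculation). Visits at 0, 0.5 and 1 year in the intervention year. Groups of 43, 45 and 53 (Table 1).

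**Assumptions.** The article gives no within-person error SD (sigma), no between-person SD of true slopes (tau), no correlation of a person's true slope across phases (rho) and no spacing of the pre-phase visits. I take annual visits (annual follow-up is mentioned only for the usual-lifestyle group, who are "encouraged to participate in annual follow–up assessments"), independent errors, and rho = 1 unless stated.

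**The plan's own figure.** A normal approximation gives 2 × (1.960 + 0.842)² × 8²/5² = 40.2, so 41 per arm and 82 in total. The noncentral t calculation gives 41.17, so 42 per arm and 84. The stated 84 is reproduced, and 8 is the SD it rests on.

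**Step 1: weight of the baseline value.** In a least-squares slope, the visit at time t has weight (t − mean)/Sxx.
- Pre-phase −6 to 0: mean −3, Sxx = 28, baseline weight 3/28 = 0.107, error variance sigma²/28.
- Intervention year 0, 0.5, 1: mean 0.5, Sxx = 0.5, weights −1, 0, +1, error variance 2 sigma².
- Covariance from the shared error: −(3/28) sigma².

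**Step 2: the coefficient.**
- Baseline shared: b = (rho tau² − 3 sigma²/28) / (tau² + sigma²/28).
- Baseline excluded (visits −6 to −1, Sxx = 17.5): b = rho tau² / (tau² + sigma²/17.5).
- A slope SD of 8 fixes sigma² = (64 − tau²)/2.

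Example, tau = 1: sigma² = 31.5. Shared: (1 − 3.375)/(1 + 1.125) = −1.12. Excluded: 1/(1 + 1.8) = 0.36.

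**Step 3: break-even.** With rho = 1, b = 0 when tau² = (3/28)(64 − tau²)/2, so tau² = 3.43/1.054 = 3.25 and tau = 1.8. With a slope SD of 4, tau² = 0.857/1.054 = 0.81 and tau = 0.9. With SD 8, break-even is 2.5 at rho = 0.5, and 2.07 for a five-year pre-phase that still includes baseline.

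**Step 4: what is left of a true slope difference of 1.0** that is equal in both phases, with no treatment effect (1 − b; simulated values for 88 versus 53, 2,000 runs, in brackets):

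| tau | b, shared | left, shared | b, excluded | left, excluded |
|---|---|---|---|---|
| 0.5 | −2.28 | 3.28 (3.22) | 0.12 | 0.88 (0.83) |
| 1 | −1.12 | 2.12 (2.06) | 0.36 | 0.64 (0.63) |
| 1.5 | −0.32 | 1.32 (1.37) | 0.56 | 0.44 (0.46) |
| 2 | +0.15 | 0.85 (0.85) | 0.70 | 0.30 (0.30) |
| 3 | +0.61 | 0.39 (0.39) | 0.85 | 0.15 (0.12) |

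**Step 5: does the ranking depend on the unknowns?** The fraction left is:
- shared: [(1 − rho) tau² + sigma²/7] / [tau² + sigma²/28]
- excluded: [(1 − rho) tau² + sigma²/17.5] / [tau² + sigma²/17.5]

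The shared version has the larger numerator and the smaller denominator, so it leaves more for every positive tau and sigma and every rho.

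**Step 6: the randomised contrast.** Simulated at 43 versus 45, tau = 1 and no true effect, the coefficient is again −1.11, but the adjusted difference averages 0.03. There is no bias. On precision, the residual variance is 64 − cov²/var:
- tau = 0.5: 64 − 3.165²/1.388 = 56.8 shared, 64.0 excluded; SE about 6% larger when excluded (square root of 64.0/56.8 = 1.06).
- tau = 1: 64 − 2.375²/2.125 = 61.3 shared, 63.6 excluded; SE about 2% larger.
- tau = 2: 63.9 shared, 61.2 excluded; SE about 2% smaller.

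**The case against.** **The overlap is inferred.** The article names no visits and gives no trial baseline date, and the Introduction's five years would fit a pre-phase ending one annual visit earlier. A reader might infer that the plan fixes a shared baseline; it does not. What stands is that the Statistical analysis and Discussion sections both say six years up to the intervention, which makes sharing the natural reading. The plan has also already fixed the covariate, so this is more than a detail left to the SAP.

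**The sign is not established.** A reader might infer that the coefficient must be negative and that adjustment always makes matters worse than no adjustment. The documents do not support that. At tau of 2 or more with SD 8, the coefficient is positive. With SD 4 it is already about +0.16 at tau 1. The SD of 8 is a planning value in a calculation based on a small study of CKD patients, and the Discussion says the present participants have better-preserved kidney function. This objection stands against any unconditional claim. It does not touch Step 5: adjustment is weaker with baseline shared whatever the sign.

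**The reach is limited.** The ANCOVA is additional to the primary model. The figures describe Model 2 slopes; Model 1, described with random intercepts only, yields no participant-specific slope to use, which is a separate matter. The article never calls this ANCOVA its defence against self-selection, and it lists self-selection as a limitation. All of this stands.

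**Harm needs a real prior-slope difference.** Table 1 shows baseline levels, not prior slopes by group, so none is documented. If the usual-lifestyle group declined 0.5 per year faster, simulation gives an adjusted difference of 0.65 to 1.63 for tau 0.5 to 1.5. The excess over 0.5 is 0.15 to 1.13, against a standard error of 8 × √(1/88 + 1/53) ≈ 1.4 and a planned effect of 5. That is modest, but it is systematic and avoidable.

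**Conclusion.** The point holds in conditional form. If the trial-baseline eGFR enters both slopes, as the text most naturally reads, the ANCOVA coefficient is biased downward. It falls below zero when the true between-person slope SD is under about 1.8 mL/min/1.73 m² per year with a 1-year slope SD of 8, or under about 0.9 with an SD of 4. These thresholds assume annual visits, independent errors and stable true slopes.

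In the Model 2 ANCOVA, less of any prior-slope difference against the usual-lifestyle group is then removed than should be. Below the threshold the difference grows, roughly doubling at a true-slope SD of 1; above it, the adjustment is only too weak (85% left against 30% at a true-slope SD of 2).

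A reader might take this as a threat to the trial's main result. It is not: exercise versus stretching stays unbiased, and the primary mixed model uses no pre-intervention slope.

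**What to change.** State which visits enter each slope, and end the covariate slope at the last Aging Kidney Study value before the trial baseline, so that no eGFR value enters both covariate and outcome. One joint piecewise mixed model over all eGFR values, with a knot at baseline, is an alternative rather than a requirement. Reconcile the five-year pre-phase in the Introduction with the six-year one in Statistical analysis and the Discussion.

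The cost is about one sentence of analysis wording. The pre-slope loses one annual value and is slightly less precise (error variance sigma²/17.5 instead of sigma²/28). The randomised contrast may lose a little precision if slope heterogeneity is very low (Step 6).

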### Randomization and blinding

Participants are to be classified into one of the following three groups: (1) exercise intervention group, (2) stretching intervention (active control) group, and (3) usual lifestyle (time control) group (Fig. 2). Participants voluntarily choose to enroll in either the usual lifestyle group or one of two intervention groups (exercise or stretching). Assignment to the usual lifestyle or intervention group is determined based on participant preference and collected via a questionnaire administered after obtaining written informed consent. Only those who opt for the intervention arm are subsequently randomized into one of the two groups (i.e., exercise or stretching group). Randomization within the intervention arm is stratified by age, sex, and GFR stage and performed using a computer–generated randomization sequence following the completion of baseline assessments. The allocation ratio between the two intervention groups is 1:1. The random allocation sequence was generated by a study statistician (MG). Allocation of participants was conducted by an independent study investigator (YN) who had no direct contact with participants. Personnel involved in participant enrollment (KK) did not have access to the random allocation sequence at any stage, ensuring adequate allocation concealment. The investigators responsible for evaluating the primary outcome are independent of the study team and remain blinded to group allocation throughout the study period. However, due to the inherent characteristics of the interventions (structured exercise training versus stretching) and the need to describe the intervention procedures in the informed consent documents and study protocol, blinding participants to group allocation was not feasible. To mitigate the risk of performance bias, we standardized the frequency, duration, and monitoring procedures of both intervention programs.

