## Results

The demographic and clinical characteristics at the time of allocation of participants who completed the baseline assessment are presented in Table 1. At baseline, the exercise, stretching, and usual lifestyle groups were similar with respect to age, proportion of women, height and weight, body mass index, eGFR, blood biochemistry, blood pressure, and heart rate.

**Table 1 Tab1:** Baseline characteristics of exercise, stretching, and usual lifestyle groups

	Exercise (*n* = 43)	Stretching (*n* = 45)	Usual lifestyle (*n* = 53)
Age, years	68±9	67±10	69±9
Women, n (%)	32 (74)	32 (71)	37 (70)
Height, cm	157±6	160±10	158±8
Weight, kg	56.3±12.4	57.6±13.6	53.5±10.4
Body mass index, kg/m^2^	22.6±4.1	22.4±4.1	21.2±2.9
Serum cystatin C, mg/dL	0.84±0.19	0.85±0.21	0.92±0.35
eGFR_cys_, mL/min/1.73m^2^	85±19	86±19	81±23
Total cholesterol, mg/dL	220±39	220±37	227±44
HDL cholesterol, mg/dL	76±20	76±19	78±18
LDL cholesterol, mg/dL	122±30	117±27	126±36
Triglyceride, mg/dL	83±35	100±54	84±26
Fasting blood glucose, mg/dL	84±14	90±16	91±16
Hemoglobin A1c, %	5.44±0.43	5.53±0.53	5.48±0.45
Systolic blood pressure, mmHg	125±16	122±15	122±16
Diastolic blood pressure, mmHg	73±8	72±9	72±11
Pulse pressure, mmHg	52±11	50±9	50±9
Heart rate, bpm	60±7	60±9	62±9

Values are presented as the means ± standard deviation or frequency counts (percentage)

eGFR_cys_, estimated glomerular filtration rate calculated based on serum cystatin C levels; HDL, high–density lipoprotein; LDL, low–density lipoprotein

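### The secondary-outcome GEE keeps baseline as a freely estimated response, so the randomised exercise-versus-stretching contrasts are valid but less precise than the collected data allow

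*Protocol article*

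**What the plan says.** The Statistical analysis section gives the secondary-outcome GEE as "including group, categorical time point (baseline, 6 months, and 1 year), and their interaction term as factors". The working correlation is unstructured, with a simpler structure if that fails to converge, and results are presented as marginal means with 95% confidence intervals. No other model term is listed. The section does not say whether the test is the group-by-time interaction or a comparison of group means at a visit.

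The same section does name covariates elsewhere: baseline eGFR in the primary mixed model, and the pre-intervention slope in the analysis of covariance of slopes.

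Under Randomization and blinding: "Randomization within the intervention arm is stratified by age, sex, and GFR stage". Randomisation follows the baseline assessments. The usual-lifestyle group is chosen by the participants and is not randomised.

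On the outcomes affected, Primary and secondary outcome measures says "The secondary outcomes include alterations in renal hemodynamics and oxygenation assessed using Doppler ultrasound imaging and MRI", followed by a long list that includes vascular function, mineral and bone markers, body composition, strength and fitness.

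**The concern.** Exercise and stretching are allocated at random after baseline is measured, so the two arms share the same true baseline mean for every outcome. The planned model does not use this: it gives each arm a free baseline mean. It also omits the factors on which the randomisation was stratified.

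Two things follow for the randomised comparison. Intervals are wider than the data already collected would allow. And any chance baseline difference between 43 and 45 participants feeds into the estimate, in a direction that depends on which contrast is read.

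The outcomes concerned carry the part of the first hypothesis about renal haemodynamics and mineral metabolism (Introduction), and the mechanistic aim in the Discussion.

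**Working it through.** **The plan's own figure.** The only sample size in the article is for the primary outcome. Its inputs are a slope difference of 5 mL/min/1.73 m² per year, an SD of 8, two-sided testing at 5% and 80% power. A two-sample t-test calculation gives 41.17 per arm, rounded up to 42, so 84 in total, as stated. No power, effect or correlation is given for any secondary outcome.

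**Inputs.** Arm sizes are 43 (exercise) and 45 (stretching), from Table 1. The correlation ρ between baseline and follow-up is an assumption, shown from 0.3 to 0.9. The SD σ is taken as equal at each visit and data as complete.

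**Step 1: what the model estimates.** With group, categorical time and their interaction, the mean model is saturated. With complete data the 1-year interaction is therefore the difference between arms in mean change from baseline, whatever the working correlation. An unstructured GEE fitted to simulated data confirmed this: interaction −0.0605, difference in mean change −0.0605.

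**Step 2: precision.** The variance factors, in units of σ²(1/43 + 1/45), are:

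- change contrast: 2(1 − ρ)
- difference in 1-year means: 1
- baseline-adjusted contrast: 1 − ρ² (one lost degree of freedom ignored)

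Since √(1/43 + 1/45) = 0.213, the standard errors in SD units are:

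| ρ | Change | 1-year means | Adjusted | Excess, change | Excess, means |
|---|---|---|---|---|---|
| 0.3 | 0.252 | 0.213 | 0.203 | 24% | 5% |
| 0.5 | 0.213 | 0.213 | 0.185 | 15% | 15% |
| 0.7 | 0.165 | 0.213 | 0.152 | 8.5% | 40% |
| 0.9 | 0.095 | 0.213 | 0.093 | 3% | 129% |

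The excess is √(2/(1 + ρ)) − 1 for change and 1/√(1 − ρ²) − 1 for 1-year means.

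In power terms, take an effect that the adjusted analysis would detect with 80% power. Another contrast then has power Φ(2.80 × SE adjusted / SE other − 1.96). At ρ of 0.3, 0.5, 0.7 and 0.9 this gives 62%, 68%, 73% and 78% for change, and 76%, 68%, 52% and 23% for 1-year means.

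**Step 3: chance baseline gap.** Given an observed baseline gap g (exercise minus stretching), the change contrast shifts by −(1 − ρ)g, the 1-year-mean contrast by +ρg, and the adjusted contrast by about 0. In 1,500 simulated trials the shifts per unit of gap were −0.52, +0.48 and −0.01 at ρ = 0.5, and −0.31, +0.69 and −0.01 at ρ = 0.7.

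**Step 4: the size of gap that can occur.** Table 1 has "Fasting blood glucose, mg/dL 84±14 90±16 91±16" (exercise, stretching, usual lifestyle). The randomised arms differ by (84 − 90)/√((14² + 16²)/2) = −6/15.03 = −0.40 SD. An outcome with that gap and ρ = 0.5 would shift by 0.5 × 0.40 = 0.20 SD: upward for the change contrast, downward for 1-year means. At ρ = 0.7 the shifts are 0.3 × 0.40 = 0.12 SD upward and 0.7 × 0.40 = 0.28 SD downward.

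**The case against.** The strongest reply is that the planned model is standard and valid. Its randomised contrast is unbiased over repeated randomisations, and no stated power is missed because none is claimed for these outcomes. The Discussion calls the secondary results hypothesis-generating. Keeping baseline as a response retains participants who lack some visits, and free baseline means are right for the self-selected group. All of this stands. It limits the importance of the point, but it does not justify intervals wider than the data allow, and the constrained form below keeps the same advantages.

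A fuller analysis plan might also add covariates. That is possible for the stratification factors. But the article lists this model's terms, and it names baseline adjustment for the primary model and not here.

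Four stronger readings are tempting, and the article supports none of them:

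- **That baseline is ignored or the estimate is biased.** The change contrast subtracts baseline. It over-corrects a chance gap, which is an efficiency and conditional-imbalance problem.
- **That power can be worked out from 5/8 = 0.625 SD.** That effect and SD belong to the primary eGFR slope and say nothing about the secondary outcomes.
- **That the glucose gap distorts a planned secondary outcome.** Fasting glucose is not named as one. It is also the largest gap among those checked between the randomised arms (p about 0.065); pulse pressure and HbA1c differ by about 0.2 SD. It shows only what can occur.
- **That omitting age, sex and GFR stage has a known cost.** Their relation to the secondary outcomes is not given, so the loss cannot be quantified.

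**Conclusion.** The point holds as one of efficiency. As written, the secondary GEE gives a valid exercise-versus-stretching contrast that is less precise than a baseline-adjusted one at every correlation below 1, if change is tested. The excess in standard error runs from about 24% at ρ = 0.3 to about 3% at ρ = 0.9, so the gain is modest for highly stable measures. If 1-year marginal means are compared, the ordering reverses and the loss is largest for those same stable measures. Because the article does not fix the contrast, neither case can be excluded.

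These sizes rest on an assumed ρ, equal variances across visits and complete data. The outcomes are hypothesis-generating, so this is an improvement worth making, and it does not threaten the trial's primary conclusion.

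**What to change.** For exercise versus stretching, use one of two forms:

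1. Model the 6-month and 1-year values with group, visit, group × visit, the outcome's own baseline value and baseline × visit.
2. Keep baseline as a response and constrain the two randomised arms to a common baseline mean. This also keeps participants with a missing baseline value. The fallback working correlation should then not be independence, because the contrast would revert to the raw follow-up difference.

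In either form, add the stratification factors (age, sex, GFR stage). State that the reported contrast is the adjusted between-arm difference, with its 95% confidence interval, at each visit. Leave the usual-lifestyle group's baseline mean unconstrained, because participants chose that group and equal baseline means cannot be assumed.

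The cost is slightly more analysis work and a short change of wording, with no new data. The covariate form also needs a rule for missing baseline values.
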